## Abstract

**Background:**

Regional anticoagulation with citrate is the recommended first line treatment for patients receiving continuous renal replacement therapy (CRRT). There is wide variability in filter patency which may be due to differences in patient characteristics and local practice. It is also possible that citrate has effects on primary and secondary haemostasis, fibrinolysis and platelet function that are still unknown. The primary aim of the study is to describe the effect of citrate on coagulation and fibrinolysis pathways in both the patient and the haemodialysis circuit.

**Methods:**

The study will recruit 12 adult patients admitted to the intensive care unit, requiring CRRT with regional citrate anticoagulation for acute kidney injury. Patients with pre-existing thrombotic or bleeding tendencies will be excluded. Thrombin generation, clot lysis and platelet function will be measured at baseline and at 12, 24, 36, 48 and 72 h after commencing CRRT (from the patient and from the circuit). We will describe the evolution of parameters over time as well as the differences in parameters between the patient and the circuit.

**Discussion:**

The study will provide new data on the effects of citrate during continuous renal replacement therapy which is not currently available. We will minimise confounding factors through the use of tight exclusion criteria and accept that this will slow down recruitment. Depending on the results, we hope to incorporate the findings into existing clinical guidelines and clinical practice with the aim to prevent premature filter clotting and interruptions in treatment.

**Trial registration:**

The study was registered with clinicaltrials.gov on 10th June 2015 (NCT02486614).

## Background

Citrate has emerged as the recommended first line anticoagulant for continuous renal replacement therapy (CRRT) in the Intensive Care Unit (ICU) based on its efficacy and safety profile [1]. It acts by chelating calcium and inhibiting the blood coagulation chemistry at several levels (Fig. 1). Several randomized controlled trials have shown significantly longer filter patency with citrate compared to anticoagulation with heparin [2]. However, the reported circuit life with citrate anticoagulation varies from a mean of 16 h to 125 h [2]. The exact reasons for this variation are not clear but are likely to be multifactorial.

**Fig. 1 Fig1:**
[figure not shown]
Known effects of citrate on clotting pathways

Patient characteristics and vascular access problems are important risk factors for premature clotting. In fact, in patients with acute kidney injury (AKI) and sepsis, the coagulation/fibrinolysis balance is often deranged even prior to starting CRRT [3, 4]. A proportion of patients may also have an underlying medical condition that predisposes them to the formation of clots, such as Protein C deficiency or anti-phospholipid syndrome. In addition, no anticoagulant is effective at inhibiting all steps of the coagulation pathway completely. For instance, whilst citrate reduces thrombin generation by inhibiting reactions upstream, it does not impact all effects of thrombin (Fig. 1). It is also unknown whether citrate has any clinically important direct or indirect effects on fibrinolysis or platelet function [5–7]. Finally, not all events within the circuit are represented by systemic clotting results, and it has been argued that coagulation and fibrinolysis need to be studied separately in the patient and in the extracorporeal circuit [8]. We report our protocol to study the effects of citrate on coagulation and fibrinolysis pathways. (Version 1.1, 26 February 2014).

## Methods/design

### Aims

Our aim is to perform a detailed evaluation of the effects of citrate on the coagulation and fibrinolysis pathways during CRRT. The primary objective is to determine changes in primary haemostasis, coagulation and fibrinolysis parameters from baseline within the patient’s systemic circulation and the CRRT circuit over the course of 72 h of regional anticoagulation with citrate. The outcomes are parameters reflecting the coagulation and fibrinolysis pathways (see below).

### Design

We plan to conduct a prospective observational cohort study.

### Setting

The study is conducted in the critical care unit in a tertiary care centre in the United Kingdom.

### Patient selection

Patients with AKI in whom the treating team intend to commence on CRRT with citrate anti-coagulation will be screened against the inclusion and exclusion criteria. Patients meeting all of the inclusion criteria and none of the exclusion criteria will be recruited.

The inclusion criteria are:admitted to the critical care unittreating clinician plans to initiate CRRT with regional citrate anticoagulationage > 18 yearsexpected to require CRRT for >72 harterial or central venous catheter in situ to allow blood sampling

Exclusion criteria are:known pre-existing thrombotic tendencyknown pre-existing bleeding tendencydisseminated Intravascular Coagulation (DIC)transfusion of any blood products in the 24 h before enrolmentactive bleeding (ie. needing blood transfusion) at time of enrolmenthaemoglobin at time of enrolment <75 g/Lhaematocrit at time of enrolment >0.55 L/Lpatient would refuse red blood cell transfusion (for example Jehova’s Witness)platelet count at time of enrolment <100 × 10^3^/μLtreatment with any anticoagulant or antiplatelet agent at enrolment or within 7 days of enrolment with the exception of heparin or low molecular weight heparin for deep venous thromboembolism (DVT) prophylaxisintravenous heparin exposure within 4 h of commencing citrate anticoagulationmalnourishment, ie. body mass index (BMI) <18.5 kg/m^2^ or unplanned weight loss >10% actual body weight (ABW) in preceding 6 months or BMI <20 kg/m^2^ and unplanned weight loss >5% ABW in preceding 6 months.CRRT prescribed for an indication other than acute kidney injury

### Sample size calculation

A formal sample size calculation was not possible due to lack of data in the literature. Following discussion with experts in the field, a sample size of 12 participants with complete data for 48–72 h was considered to be adequate to gain better understanding of coagulation and fibrinolysis during citrate based CRRT and to inform the design of future studies.

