### Withdrawal criteria

Patients will be excluded from the study at their own request or the request of their legal representative. They will be excluded from further blood sampling if any of the following events occur during the 72 h sampling period:Development of Disseminated Intravascular Coagulation (DIC).Need for treatment with any systemic anticoagulant or antiplatelet agent with the exception of heparin or low molecular weight heparin for DVT prophylaxisNeed for treatment with platelets or clotting factors

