### Statistical analysis

The baseline characteristics will be summarised using appropriate descriptive statistics [i.e. frequency (percentage) for categorical data and mean (standard deviation) or median (interquartile range) for continuous data]. All coagulation and fibrinolysis parameters at baseline will be summarised as means (standard deviation) unless the distribution is highlight skewed, in which case median values (interquartile range) will be used.

Average coagulation and fibrinolysis parameters at each time point, and the mean (standard deviation) of the difference relative to baseline will be presented. The evolution of parameters will also be illustrated graphically by plotting the mean (with 95% confidence interval) against time points. Trajectories of individual patients over time will be shown graphically. Separate figures will be used to summarise data obtained from bloods taken from the patient and that from the CRRT circuit.

Repeated measures analysis of variance (ANOVA) (one for each of the parameters obtained from patient’s bloods and separately for those from the circuit), will be used to further explore changes in parameters over time. Where CRRT ends before 72 h patients will not have measurements taken at 72 h. The ANOVA will therefore include all measurements up to 48 h (unless all patients have complete data to 72 h, in which case the final time point will also be included). If a main effect of time is identified, post-hoc comparisons will be carried out to determine where differences lie.

Coagulation and fibrinolysis parameters from the patients’ blood will be plotted against the corresponding value obtained from blood drawn from the CRRT circuit. The mean (standard deviation) of the differences will be calculated overall and at each time point and Bland-Altman limits of agreement calculated.

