## Discussion

To our best knowledge, this is the first study that will provide a detailed description of clotting and fibrinolysis processes before CRRT and the effects of citrate on coagulation pathways, fibrinolysis and platelet function during CRRT.

The strengths of this project are:i)The project will provide data that are currently not available.ii)By using very tight inclusion and exclusion criteria we are minimising confounding influences as much as possible.iii)Serial blood samples will be taken from the systemic circulation and the CRRT circuit separately to differentiate between events in the patient and in the extracorporeal circuit.iv)The results have potential to inform the design of future exploratory studies and intervention trials aimed a prolonging circuit life during CRRT and preventing unplanned interruptions in treatment.

We are aware of potential limitations and risks of the project which we will eliminate as much as possible.i)As a result of very strict criteria for inclusion, exclusion and withdrawal and a relatively long sampling period, recruitment is likely to be slow.

It is possible that we identify medical problems through this research that may have implications for patients and their close relatives, for instance a genetic predisposition to clotting which was previously not known about. With approval by the Research Ethics Committee, we have put measures in place to make sure that affected patients and relatives will receive the necessary medical attention.

Depending on the findings of the study, we plan to incorporate the results into current guidelines and clinical practice and hope that premature filter clotting can be prevented and the delivery of CRRT improves.

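### The sample size is 12 recruited in one place and 12 with complete data in another, and patients lost before 48 h have no stated place in the repeated measures ANOVA

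*Protocol article*

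**What the plan says.** The Methods part of the abstract states: "The study will recruit 12 adult patients admitted to the intensive care unit". The section Sample size calculation gives the reason for the number. It says that "A formal sample size calculation was not possible due to lack of data in the literature" and that, on expert advice, "a sample size of 12 participants with complete data for 48–72 h was considered to be adequate". No power, effect size, standard deviation or loss rate stands behind the 12.

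The section Withdrawal criteria provides for loss in two ways. Patients may leave on request: "Patients will be excluded from the study at their own request or the request of their legal representative". Sampling also stops on certain events: "They will be excluded from further blood sampling if any of the following events occur during the 72 h sampling period". The listed events are DIC, need for a systemic anticoagulant or antiplatelet agent (prophylaxis of deep venous thrombosis excepted), and need for platelets or clotting factors.

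The section Statistical analysis deals with one kind of incomplete data: "Where CRRT ends before 72 h patients will not have measurements taken at 72 h". For that reason the repeated measures ANOVA stops at 48 h unless everyone is complete to 72 h. The section does not say what happens to a patient lost before 48 h.

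**The concern.** The number recruited and the number with complete data are different quantities. The 12 rests on expert judgement alone, so what it counts is the whole of the justification. A reader cannot tell whether the study stops at 12 enrolled, whatever the loss, or goes on enrolling until 12 are complete.

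The choice also affects what the results describe. DIC and a need for platelets or clotting factors are disturbances of the system that the primary objective sets out to measure, so loss for these reasons may be informative. A conventional repeated measures ANOVA needs a full set of time points from each patient and would drop anyone withdrawn before 48 h. Enrolling replacements restores the count, but the 12 analysed would still be those who stayed free of these events.

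**Working it through.** **Inputs from the protocol article.** 12 recruited (abstract). 12 with complete data for 48–72 h (Sample size calculation). ANOVA to 48 h (Statistical analysis). Expected duration of renal replacement above 72 h as an inclusion criterion (Patient selection).

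**Input not in the documents.** The proportion *d* lost before 48 h. I assume 5%, 10% and 20%, with independent losses of equal probability.

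**Step 1: the plan's own figure.** The 12 comes from expert discussion and has no formula, so it can be neither reproduced nor refuted. The check concerns only what the 12 counts.

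**Step 2: which losses count.** The target accepts data complete to 48 h, and the ANOVA ends there. Loss between 48 and 72 h therefore does not count against the target; only loss before 48 h does.

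**Step 3: if exactly 12 are recruited.** The probability that all 12 are complete is (1 − *d*)^12, and the expected number complete is 12(1 − *d*).

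**Step 4: if 12 complete patients are wanted.** The number to recruit for 12 expected complete is 12/(1 − *d*), rounded up. The last column gives the smallest number recruited with at least an 80% binomial chance of 12 or more complete.

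| Assumed loss before 48 h | P(12 of 12 complete) | Expected complete | Recruits for 12 expected complete | Recruits for 80% chance of 12 |
|---|---|---|---|---|
| 5% | 0.95^12 = 0.54 | 11.4 | 12/0.95 = 12.6, so 13 | 13 |
| 10% | 0.90^12 = 0.28 | 10.8 | 12/0.90 = 13.3, so 14 | 14 |
| 20% | 0.80^12 = 0.07 | 9.6 | 12/0.80 = 15 | 17 |

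The chance of 12 complete patients falls below one half once *d* exceeds 1 − 0.5^(1/12) = 0.056.

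**Step 5: precision.** The half-width of a 95% confidence interval for a mean change, in units of the SD of the change, is t(0.975, n − 1)/√n. At n = 12 this is 2.201/3.464 = 0.64. At n = 8, which is what 12 recruits leave if one third are lost, it is 2.365/2.828 = 0.84.

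**Step 6: who remains in each analysis.** The withdrawal criteria end further sampling but do not discard samples already taken. The means, differences from baseline and individual trajectories in Statistical analysis are not limited to complete patients. The selection therefore bears mainly on the ANOVA and its post-hoc comparisons, and on the later time points of the summaries, where withdrawn patients no longer contribute.

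**The case against.** Several points on the other side stand.

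- The abstract may be shorthand for the sample size section, and the Discussion suggests continued enrolment: "As a result of very strict criteria for inclusion, exclusion and withdrawal and a relatively long sampling period, recruitment is likely to be slow". Withdrawal slows recruitment only if withdrawn patients are to be made up. This is a hint, not a rule, and it leaves the two statements unreconciled.
- Early end of treatment is largely covered, by the inclusion criterion of more than 72 h expected and by the 48 h limit of the ANOVA.
- Stopping sampling once other agents act on the measured parameters is a stated choice to limit confounding. That choice is not at issue here. The question is how patients it affects enter the analysis.
- Not all loss is related to outcome: withdrawal on request need not be, nor need treatment with an anticoagulant or antiplatelet agent.

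A reader might infer that 12 recruits cannot deliver 12 complete patients. The documents give no loss rate, so a shortfall is likely under modest assumptions but is not shown. A reader might also infer that the results must lean towards finding no disturbance on citrate. That would require knowing that the lost patients differ in one direction and that the difference is an effect of citrate, and the documents say neither. Nor are power calculations relevant, since the study is descriptive and sets no power target.

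**Conclusion.** The point holds as an inconsistency in the study's only design number, together with a gap in the ANOVA. That the two definitions differ is certain from the text. Its consequence depends on assumed loss: with 12 recruited, the chance of 12 complete to 48 h is 0.54, 0.28 and 0.07 at 5%, 10% and 20%. Where 12 expected complete patients are wanted, the extra recruitment is small at these rates, one to three patients.

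The selection argument holds in a limited form. An ANOVA of patients complete to 48 h describes those who avoided the withdrawal events, some of which are related to the outcomes. Neither the direction nor the size of any resulting bias can be derived from the documents. The change should be made, but the point does not invalidate the study.

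**What to change.** State the same quantity in the abstract and in the sample size section, in one of two forms:

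- 12 enrolled, with the precision at the number expected to be complete (for reference, a half-width of 0.64 SD at n = 12 and 0.84 SD at n = 8); or
- 12 complete to 48 h, with the expected number enrolled and a statement that enrolment continues until 12 are complete.

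Analyse change over time with all samples from every enrolled patient up to withdrawal, for example with a linear mixed model with time as a categorical factor. Keep the completers-only ANOVA as a sensitivity analysis. The mixed model uses the early samples of withdrawn patients, but it relies on loss being explained by the values already observed, and this should be stated as a limitation. Tabulate withdrawals by reason and time.

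The withdrawal rules and the sampling schedule need no change. The cost is a few sentences, one table, slightly more analysis work, and a stated size or precision that looks less favourable.

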### Blood sampling

#### Baseline

The following blood tests will be performed at baseline, i.e. immediately prior to commencing CRRT: Full Blood Count (FBC), prothrombin time (PT), activated partial thromboplastin time ratio (APTTr), fibrinogen, D-Dimers, antithrombin activity, protein C activity, free protein S antigen, resistance to activated protein C (APCR) screening, homocysteine, PT 20210 mutation test, factor VIII activity, von Willebrand factor antigen, Dilute Russell’s Viper Venom Time (DRVVT), Dilute Activated Partial Thromboplastin Time (DAPTT), anticardiolipin antibodies, anti-beta 2 glycoprotein I antibodies, thrombin generation assay, clot lysis, prothrombin fragment 1 + 2, thrombin-antithrombin complexes (TAT) enzyme linked immunosobent assays (ELISA) and platelet function screening.

#### During CRRT

At 12, 24, 36, 48 and 72 h after commencing CRRT, blood samples will be taken from the systemic circulation and from the CRRT circuit to measure the following parameters: FBC, PT, APTTr, fibrinogen, D-Dimers, thrombin generation assay, clot lysis and platelet function screening.

### Laboratory tests

All laboratory tests except FBC will be conducted in the Haemostasis & Thrombosis Laboratories at Guy’s & St Thomas’ Hospital. Dade® Innovin® recombinant thromboplastin, Actin FS®, Thromboclotin®, Thrombin-Reagent®, Innovance D-dimer and HYPHEN BioMed Biophen FVIII:C chromogenic assay (Siemens Healthcare, Marburg, Germany) will be used on Sysmex CS2100i coagulation analysers (Sysmex UK, Milton Keynes, UK) for PT, APTT, Clauss fibrinogen, D-dimers and FVIII activity respectively. For lupus anticoagulant detection, DRVVT will employ Life Diagnostics LA Screen and LA Confirm reagents (Diagnostica Stago UK, Theale, UK), and DAPTT will use Stago PTT-LA (Diagnostica Stago) in the screen and addition of Bio/Data Corporation LA Confirmation Reagent (Alpha Labs, Eastleigh, UK) for the confirm. LA assays will be performed on a Sysmex 2000i analyser (Sysmex UK). Chromogenix Coamatic antithrombin, Coamatic protein C, Coatest APC Resistance, Coatest APCR resistance-V (Quadratech Diagnostic Ltd., Epsom, UK) and STA®-Liatest® Free protein S (Diagnostica Stago) will be used on Sysmex CS2000i analysers for antithrombin activity, protein C activity, phenotypic activated protein C resistance and free protein S antigen respectively. Inova Diagnostics QUANTA Lite® (ELISA) kits for IgG and IgM anticardiolipin and anti-β_2_ glycoprotein I antibodies (Werfen UK, Warrington, UK), Enzygnost® F1 + 2 and TAT will be performed on a Dynex DS2 ELISA analyser (Werfen UK) for anticardiolipin antibodies, anti-β_2_ glycoprotein I antibodies, prothrombin fragment 1 + 2 and thrombin-antithrombin complexes respectively. HemosIL VWF Antigen will be performed on an ACL TOP 500 coagulation analyser (Werfen UK) for von Willebrand factor antigen. Platelet function screening will be performed on a PFA-100 analyser (Sysmex UK) with collagen/ADP and collagen/epinephrine cartridges (Sysmex UK). Homocysteine will be assayed with Abbott ARCHITECT chemiluminescent microparticle assay (Abbott UK, Maidenhead, UK) on an Abbott ARCHITECT *i*2000SR immunoassay analyser (Abbott UK). The Thrombin Generation Assay will performed using a Technoclone kit (Technoclone, Vienna, Austria) on a Wallac Victor^3^ multilabel plate reader (Perkin Elmer, Turku, Finland). The Clot Lysis Assay will be performed as previously described [6] and read on a Wallac Victor^3^ multilabel plate reader (Perkin Elmer, Turku, Finland). The Prothrombin 20,210 polymorphism will be screened for using an in house developed allelic discrimination assay on an Applied Biosystems 7500 Real-Time PCR System (Applied Biosystems, Foster City, CA, USA).

### Baseline data collection

The following data will be collected: age, gender, ethnicity, admission diagnosis, comorbidities, biochemistry profile, C-reactive protein (CRP), Acute Physiology and Chronic Health Evaluation (APACHE) II score on admission and daily Sequential Organ Failure Assessment (SOFA) scores.

### Withdrawal criteria

Patients will be excluded from the study at their own request or the request of their legal representative. They will be excluded from further blood sampling if any of the following events occur during the 72 h sampling period:Development of Disseminated Intravascular Coagulation (DIC).Need for treatment with any systemic anticoagulant or antiplatelet agent with the exception of heparin or low molecular weight heparin for DVT prophylaxisNeed for treatment with platelets or clotting factors

### Statistical analysis

The baseline characteristics will be summarised using appropriate descriptive statistics [i.e. frequency (percentage) for categorical data and mean (standard deviation) or median (interquartile range) for continuous data]. All coagulation and fibrinolysis parameters at baseline will be summarised as means (standard deviation) unless the distribution is highlight skewed, in which case median values (interquartile range) will be used.

Average coagulation and fibrinolysis parameters at each time point, and the mean (standard deviation) of the difference relative to baseline will be presented. The evolution of parameters will also be illustrated graphically by plotting the mean (with 95% confidence interval) against time points. Trajectories of individual patients over time will be shown graphically. Separate figures will be used to summarise data obtained from bloods taken from the patient and that from the CRRT circuit.

Repeated measures analysis of variance (ANOVA) (one for each of the parameters obtained from patient’s bloods and separately for those from the circuit), will be used to further explore changes in parameters over time. Where CRRT ends before 72 h patients will not have measurements taken at 72 h. The ANOVA will therefore include all measurements up to 48 h (unless all patients have complete data to 72 h, in which case the final time point will also be included). If a main effect of time is identified, post-hoc comparisons will be carried out to determine where differences lie.

Coagulation and fibrinolysis parameters from the patients’ blood will be plotted against the corresponding value obtained from blood drawn from the CRRT circuit. The mean (standard deviation) of the differences will be calculated overall and at each time point and Bland-Altman limits of agreement calculated.

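### The circuit has no baseline sample, so its planned change from baseline mixes a patient-to-circuit difference with change over time

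*Protocol article*

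**What the plan says.** Four parts of the protocol article bear on this.

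- **Aims.** The primary objective concerns changes in "parameters from baseline within the patient’s systemic circulation and the CRRT circuit over the course of 72 h". Change from baseline is asked for at both sites.
- **Blood sampling.** On baseline: "The following blood tests will be performed at baseline, i.e. immediately prior to commencing CRRT". On later samples: "At 12, 24, 36, 48 and 72 h after commencing CRRT, blood samples will be taken from the systemic circulation and from the CRRT circuit". Two-site sampling is described only for these later times.
- **Abstract, Methods.** Parameters are "measured at baseline and at 12, 24, 36, 48 and 72 h after commencing CRRT (from the patient and from the circuit"). The bracket could be read as covering baseline too, but the Baseline section rules that out: before CRRT starts there is no patient blood in the circuit.
- **Statistical analysis.** "Average coagulation and fibrinolysis parameters at each time point, and the mean (standard deviation) of the difference relative to baseline will be presented". Baseline is not defined for circuit values. Repeated measures ANOVAs follow, "one for each of the parameters obtained from patient’s bloods and separately for those from the circuit", using all measurements up to 48 h, or to 72 h if every patient has complete data. The section also plans paired patient-circuit differences, overall and at each time point, with Bland-Altman limits of agreement.

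**The concern.** The objective and the change-from-baseline summary presuppose a reference value that the sampling schedule cannot supply for the circuit. The analyst has to borrow the patient's pre-CRRT value, and the first comparison then crosses from one sampling site to another. Any steady difference between sites, for example from dilution by solution infused into the circuit, is counted as change since baseline.

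Separating events in the patient from events in the circuit is one of the strengths listed in the Discussion, and the authors hope to carry the results into guidelines. A circuit summary that cannot tell a site difference from an evolution over time works against that purpose.

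**Working it through.** **1. What the circuit summary estimates.** For one patient and one parameter, let P0 be the pre-CRRT patient value, Pt the patient value at time t, and Ct the circuit value at time t (t = 12, 24, 36, 48, 72 h). C0 does not exist. The only available circuit change from baseline is

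Ct − P0 = (Ct − Pt) + (Pt − P0),

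that is, the site difference at t plus the systemic change at t. If nothing changes over time and the circuit differs from the patient by a constant d, then Pt − P0 = 0 on average and the summary equals d at every time point. Simulated means confirm this: 0.5, 1.0, 1.5 and 2.0 SD at each of 12, 24, 36 and 48 h for those values of d.

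**2. What the circuit ANOVA tests.** The text does not list its time levels, so there are two cases:

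- (a) circuit samples only: 12, 24, 36 and 48 h, four levels;
- (b) the patient's pre-CRRT value added as a first level: five levels.

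Inputs: n = 12 (Sample size calculation section). The documents give no alpha, SD or offset. Assumed: alpha 0.05, within-patient SD 1, spherical errors, no true change over time, constant offset d.

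In case (b) the level means are (0, d, d, d, d), with grand mean 0.8d. Their sum of squared deviations is 0.64d² + 4 × 0.04d² = 0.8d². The noncentrality parameter is 12 × 0.8d² = 9.6d², with 4 and 44 degrees of freedom. In case (a) all means equal d, so the noncentrality is 0 whatever d is.

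| Offset d (within-patient SD) | Noncentrality, case (b) | Rejection, case (b), exact | Rejection, case (b), simulated | Rejection, case (a), simulated |
|---|---|---|---|---|
| 0 | 0 | 0.050 | 0.049 | 0.048 |
| 0.5 | 2.4 | 0.183 | 0.182 | 0.049 |
| 1.0 | 9.6 | 0.642 | 0.643 | 0.049 |
| 1.5 | 21.6 | 0.958 | 0.958 | 0.049 |
| 2.0 | 38.4 | 0.999 | 0.999 | 0.051 |

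The simulated columns use 40,000 data sets per row.

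**3. Reading the results.** In case (a) a constant offset does no harm, but the hypothesis is equality of circuit means from 12 h onward, so the test says nothing about change from baseline. In case (b) the offset appears as a main effect of time. The planned post-hoc comparisons would show baseline differing from all later times, with no trend afterwards. A real change completed within 12 h would give the same pattern.

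**The case against.** The strongest reply has four parts.

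**The ANOVA as worded is sound.** Separate models for circuit bloods most naturally means circuit samples only, which is case (a). This stands. A reader might infer that the planned circuit ANOVA is itself confounded by the site offset. The document does not say that the patient baseline enters that model, so the inflated rejection rates are conditional on a choice that it neither states nor excludes.

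**The circuit contrast can be calculated.** Each patient has a pre-CRRT value, it is the only state before citrate exposure, and it could serve as a common reference. This also stands. A reader might conclude that half of the primary objective is not estimable, but that is too strong. The contrast exists; what is wrong is reading it as change within the circuit.

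**Paired differences are already planned at each time point.** They estimate Ct − Pt, the component needed to separate site from time. This softens the problem. It does not remove it, because the plan ties these differences neither to the circuit's change-from-baseline summary nor to the objective.

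**This is detail for a fuller document, in a 12-patient observational study.** A list of ANOVA levels alone could be left to an analysis plan. A primary objective that calls for a circuit baseline, beside a schedule that cannot provide one, is a conflict within this document. The small descriptive design limits the consequences but does not resolve the conflict.

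**Conclusion.** The point holds in this form: the primary objective and the change-from-baseline summary extend to the circuit, the sampling schedule gives the circuit no baseline, and the resulting contrast combines site difference with systemic change. That follows from the schedule and the identity in step 1 of the working, without numerical assumptions. With no change over time, the whole offset is reported as change from baseline at every time point.

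The ANOVA part is weaker. On the natural reading its error rate stays near 5%, and its limitation is that it starts at 12 h. The 18%, 64% and 96% figures are illustrations that apply only if the patient baseline is added as a level. They rest on assumed offsets of 0.5, 1.0 and 1.5 within-patient SD, alpha 0.05 and spherical errors. The documents do not show how large the real offset is for any parameter.

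**What to change.** Change the wording as follows.

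1. State that the pre-CRRT sample is the baseline of the systemic series only.
2. Name the time levels of the circuit ANOVA as circuit samples only: 12 to 48 h, or to 72 h if all patients are complete.
3. Make the paired difference, circuit minus simultaneous patient value, and its time course the circuit estimand. The data and the calculation are already planned.
4. If circuit minus pre-CRRT patient value is still shown, label it as combining site difference and systemic change.
5. Reword the objective to match: change from baseline in the patient; patient-circuit difference and its course over time for the circuit. Make clear in the Abstract that two-site sampling begins at 12 h.

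Optional sensitivity analysis: for concentration parameters such as fibrinogen, D-dimers and platelet count, also report circuit values corrected for dilution by the paired haematocrit ratio. Full blood count is already scheduled at both sites each time.

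The cost is a few sentences in the Aims, Abstract and Statistical analysis sections. No new samples or patients are needed.
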